#### Eligibility

Patients eligible for enrolment in this clinical trial are those suffering from PDPH due to epidural analgesia, combined spinal-epidural analgesia, or spinal anaesthesia for childbirth.

The headache characteristics should be as follows:
within 5 days after deliveryrelieved in the supine position and/or worse while sitting or standingintense (NRS > 3/10)with or without: neck stiffness, tinnitus, hypoacusia, photophobia, visual impairment, nausea or vomitingafter having eliminated differential diagnosis for pre-eclampsia or eclampsia, cerebral venous thrombosis, migraine.

Patients must be at least 18 years old and benefit from healthcare insurance. They also have to provide a written informed consent.

#### Exclusion criteria

Exclusion criteria are as follows:
diplopia (which requires an epidural blood patch without delay)contraindication to ACTH: uncontrolled arterial hypertension, uncontrolled diabetes mellitus, acute psychosis, infectious diseasescontraindication to tetracosactide:
○ currently receiving a drug associated with an increased risk of Torsades de Pointes (astemizole, bepridil, IV erythromycin, halofantrine, pentamidine, sparfloxacine, sultopride, terfenadine or vincamine)○ patient received a live vaccine in the month prior to inclusionprevious history of hypersensitivity to tetracosactidepatient who has received tetracosactide since childbirthcontraindication to epidural blood patch: HIV, HVC, leukocytosis, feverpre-eclampsia or eclampsia during the current pregnancy (may be confounding for the aetiology of headache)patient who has already received a prophylactic blood patch (at the time of accidental dural puncture diagnosis)Under 18 years old or adult under guardianshipMental disorder which does not allow informed consentPatients who are enrolled in another clinical trial

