As described by Vandam and Dripps, as early as 1956 [20], the main cause of PDPH appeared to be intracranial hypotension by leakage of cerebrospinal fluid (CSF). CSF is critical in reducing impacts between the brain and the cranium during orthostatism, and the loss of this cushioning leads to headaches. Furthermore, the cerebral and meningeal vessels are stressed by the downward displacement of the brain during orthostatism. This caudal traction activates the stretch-sensitive receptors of the trigeminal nerves (frontal headache), glosso-pharyngeal and vagus nerves (occipital headache) [11, 21, 22], and the first three cervical nerves (arm pain or neck pain) [23]. According to the Monro-Kellie theory, headaches may also be related to painful venous and arterial cerebral vasodilation, which compensates for decreased CSF volume [3, 21]. In the inner ear, hypotension of the perilymph also causes an imbalance between endolymph and perilymph itself, thereby leading to hearing impairment, tinnitus and/or vertigo [16, 24].

In most cases, dural puncture closes spontaneously without consequence. PDPH is reported to resolve in more than 50% of patients within 4 days, and in more than 70% within a week. However, headache may persist in a limited number of patients [3, 20]. PDPH can limit patients’ activity, increase the duration of hospital stay and use of care [25] and is particularly disabling during the postpartum period, when the mother has to take care of her child. It is therefore important to treat this syndrome. Epidural blood patch is currently the gold standard and most effective treatment for PDPH. However, the timing for this treatment remains uncertain. Some studies have suggested a greater risk of failure when administering an early blood patch, although no causal link could be established [26–28]. The diminished effectiveness in this case, could be explained by the severity of the CSF leak [28]. Conversely, administering a delayed blood patch could increase bed rest duration. A delay of 24 to 36 h between the onset of headaches and the completion of a blood patch seems reasonable. However, delaying the blood patch by more than 48 h is not recommended [29].

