## Methods/Design

### Aim of the study

The aim of this study is to assess the efficacy and safety of tetracosactide (Synacthen®) in the treatment of post-dural puncture syndrome for patients who received neuraxial anaesthesia during childbirth.

Our working hypothesis is that a single intravenous infusion of tetracosactide may avoid the need for the epidural blood patch. To challenge this hypothesis two groups will be compared: the study group receiving an infusion of 1 mg of tetracosactide and the control group receiving a placebo (0.9% saline). Both groups receive standard analgesic treatment and epidural blood patch if needed (after a minimum of 24 h following the injection of the experimental treatment).

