### Primary endpoint

The primary endpoint of the study is the rate of epidural blood patch within a 15-day follow-up period, that is, the number of patients who receive a blood patch within the 15-day period divided by the total number of participants included.

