### Population

#### Number of patients needed

The sample size calculation is based on a previous study that investigated tetracosactide in PDPH [39] and, retrospectively, on observational data obtained from our hospital database. The primary endpoint is the rate of blood patch in the two groups. We defined the efficacy of tetracosactide as a decrease in blood patch use by 30% in the tetracosactide group, a clinically relevant difference reducing the need for invasive treatment and replacing it with an easily administered treatment that has a known safety profile.

In our centre, 90% of patients with PDPH after epidural analgesia receive a blood patch. The study reported by Hakim [39] found a greater than 50% decrease in PDPH incidence and blood patch use after prophylactic treatment with tetracosactide, in a context of epidural analgesia. We therefore need to include 44 subjects in each group, given a power of 0.80 and type I error of 0.025 (α = 2.5% Fisher’s exact test, power of 80%, p1 = 0.9; p2 = 0.6), to reduce the blood patch requirement by 30%. Thus a total of 88 patients need to be randomised.

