**Fig. 2 Fig2:**
[figure not shown]
Schedule of enrolment, intervention and assessment

Epidural blood patch is performed for patients who reported a persistent moderate to severe headache a minimum of 24 h after administration of the study treatment and 36 h after the dural puncture, based on the clinical appreciation of the anaesthesiologist. Epidural blood patch can be repeated twice if required (i.e., if the headache does not improve or if it increases again). The anaesthesiologist performs the epidural blood patch. Autologous blood is injected into the epidural space using an 18-gauge Tuohy needle. The injection is stopped when the patient feels pressure in the lower back or pain.

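### The stated reason for excluding diplopia conflicts with the minimum 24 h wait before a blood patch when diplopia first appears after randomisation

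*Protocol article*

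**What the plan says.** All references are to the protocol article.

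- **Exclusion criteria:** the first exclusion is "diplopia (which requires an epidural blood patch without delay". The parenthesis gives the reason, and the reason describes the condition itself.
- **Secondary endpoints:** diplopia is one of seven associated features whose appearance is to be described over the 15-day follow-up. The Background also names it as a symptom that may accompany the headache.
- **Aim of the study:** both groups receive standard analgesia and "epidural blood patch if needed (after a minimum of 24 h following the injection of the experimental treatment"). No exception is stated.
- **Intervention protocols (text after Fig. 2):** a patch is given for headache that persists at moderate or severe intensity, "a minimum of 24 h after administration of the study treatment and 36 h after the dural puncture". Within that condition the decision is left to judgement, being "based on the clinical appreciation of the anaesthesiologist". No other indication is named.
- **Primary endpoint:** the rate is "the number of patients who receive a blood patch within the 15-day period divided by the total number of participants included". Neither the reason for the patch nor its timing within the 15 days enters the definition.

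**The concern.** The protocol treats diplopia as a condition for which a patch cannot wait, and it foresees that diplopia may appear after randomisation. Its general rule for randomised patients nevertheless imposes a wait on any patch, whatever the need. The indication in Intervention protocols is confined to headache, so new diplopia with only mild headache has no stated route to a patch.

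Safety is what is chiefly at stake: an investigator who follows the 24 h floor literally delays a treatment that the same document says should not be delayed. Conduct is a lesser matter. The two sites could handle such a patient differently, and nothing in the article says whether a patch before 24 h is a protocol deviation or ordinary care.

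**Working it through.** **1. The sections set against one patient.** Suppose a patient enters without diplopia and it appears 6 h after the infusion, the end of the first post-treatment assessment window (2 to 6 h).

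- By the reason given under Exclusion criteria, she needs a patch without delay.
- By the Aim of the study section, the earliest patch is at 24 h, which is 24 − 6 = 18 h later.
- By Intervention protocols, the timing condition is attached to persistent headache and the decision is left to clinical judgement. That section neither provides for diplopia nor says that the minimum may be waived.
- By the Secondary endpoints section, her diplopia is recorded as an associated feature. What follows from it is not stated.

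The firm conflict is therefore between the reason under Exclusion criteria and the 24 h floor under Aim of the study. The 36 h condition is worded for headache only and adds no firm conflict.

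**2. The planned sample size, reproduced.** Inputs from Number of patients needed: "α = 2.5% Fisher’s exact test, power of 80%, p1 = 0.9; p2 = 0.6" and "We therefore need to include 44 subjects in each group". Sidedness is not stated; two-sided is taken here.

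- Mean rate (0.9 + 0.6)/2 = 0.75, difference d = 0.3, z = 2.2414 (two-sided 0.025) and 0.8416 (80% power).
- n = [2.2414·√(2·0.75·0.25) + 0.8416·√(0.9·0.1 + 0.6·0.4)]² / 0.3² = (1.3726 + 0.4835)² / 0.09 = 38.3, so 39 per arm uncorrected.
- With continuity correction: n′ = (38.3/4)·[1 + √(1 + 4/(38.3·0.3))]² = 44.7, so 45 per arm.
- Exact power of the two-sided Fisher test at 44 per arm, by enumerating all tables: 0.811.

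The stated 44 per group is reproduced. A one-sided exact test would already reach 80% at 36 per arm, so the two-sided reading fits.

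**3. How far diplopia patches could move the primary endpoint.** Expected events are 44 × 0.9 + 44 × 0.6 = 39.6 + 26.4 = 66. Most patients are thus expected to be patched anyway. If diplopia is independent of that need (an assumption), a patient patched for diplopia adds on average 1 − 0.9 = 0.1 event under placebo and 1 − 0.6 = 0.4 event under tetracosactide.

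The documents give no diplopia rate. Let a share q of each arm be patched for diplopia regardless of treatment. The rates become 0.9 + 0.1q and 0.6 + 0.4q, and the difference becomes 0.3(1 − q). Exact two-sided power at 44 per arm and alpha 0.025 is:

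| q | placebo | tetracosactide | power |
|---|---|---|---|
| 0 | 0.900 | 0.600 | 0.811 |
| 1% | 0.901 | 0.604 | 0.804 |
| 2% | 0.902 | 0.608 | 0.797 |
| 5% | 0.905 | 0.620 | 0.776 |
| 10% | 0.910 | 0.640 | 0.738 |

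The loss is small unless diplopia is frequent. The table also describes patches that are given at all, early or late. The wait itself changes only their timing within the 15 days, and it changes the count only if the need resolves before the wait is over.

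**The case against.** The strongest defence is that the exclusion acts at screening and the wait acts after randomisation. By excluding known diplopia, the protocol keeps those patients out of the wait, which is consistent at entry. A reader might infer that the protocol gives opposite instructions for the same patient; it does not. What stands is narrower: the reason given for the exclusion applies equally to diplopia that begins later, and the patch rule makes no room for it.

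A second defence is that Intervention protocols is the operative text. It is worded for persistent headache and leaves the decision to clinical judgement. This is fair as regards the 36 h condition, and a reader should not take every randomised patient with diplopia to be bound by both minimums. It does not dispose of the 24 h floor under Aim of the study, which is worded for any need. Judgement mentioned after a stated minimum can also be read as choosing whom to patch once that minimum has passed.

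Third, the article condenses a full protocol that is not shown and that may contain an exception. If it does, citing it closes the point. Until then, the finding rests on what the article states, not on an omitted detail.

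A reader might also set the 24 h wait against the Background remark that "delaying the blood patch by more than 48 h is not recommended". That does not support a finding. The remark summarises literature on a timing that the Background itself calls uncertain, and it is not a trial rule. The documents also do not give the interval from headache onset to study treatment.

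**Conclusion.** The concern holds as an unresolved conflict between a stated reason and a stated rule, for randomised patients whose diplopia begins inside the waiting period. It matters on safety grounds. How many patients would be affected is unknown, because no diplopia rate is given; listing diplopia as a descriptive endpoint shows only that it was foreseen as possible.

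A reader might infer that the primary endpoint is biased or ambiguous. The documents do not support that. Every patient patched within 15 days already counts, whatever the reason, and the analysis is by intention to treat, so calling an early patch a deviation would not change its count. Under the assumption of equal, treatment-independent diplopia patches in both arms, power falls from 0.811 to 0.797 at 2% and to 0.776 at 5%. These shares are illustrations, not estimates. The conclusion also assumes that the full protocol holds no exception to the 24 h minimum.

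**What to change.** Reconcile Aim of the study, Secondary endpoints, Exclusion criteria and Intervention protocols, so that a single rule applies to diplopia arising after randomisation and the text says whether a patch under that rule is a protocol deviation. Which rule applies is for the clinical investigators and the sponsor; this review does not propose one. If the full protocol already settles it, a cross-reference is enough.

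Record the reason for each patch and its time relative to study treatment, if the case report form does not already do so, and tabulate patches given before 24 h by arm. Leave the Primary endpoint definition as it is.

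The cost is a short clarifying amendment, at most one case report form item, and one descriptive table. The sample size is unaffected. By the Trial status section, 25 of 88 patients had been enrolled in May 2019, so 88 − 25 = 63 inclusions were still to come under the clarified rule.

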#### Consent

When a diagnosis of PDPH is made by the anaesthesiologist, screening of patients for inclusion and exclusion criteria is performed. The investigator then presents the study to the patients. Written information is provided to the patients. Patients are given some time to think before committing to the study. Final inclusion occurs shortly after they have read the information letter, raised questions they may have and signed the written informed consent.

### Randomisation, blinding, and data management

The anaesthesiologist checks the patient’s inclusion criteria and the absence of exclusion criteria. After signing of the informed consent, patients are randomised online using the ClinSight-Online software program (Ennov society, Paris, France). The randomisation list was compiled by a statistician, entered into the software and communicated to the pharmacist to prepare the numbered treatment kits. The randomization is performed by block stratification according to site. Patients are allocated to a treatment number (by the ClinSight software). The study is performed double-blinded; both patients and the medical team are blinded to treatment allocation. An anaesthetic nurse prepares the treatment according to the assigned number to which the rest of the healthcare team is blinded. Patient data are collected on electronic case report forms (eCRFs). The sponsor will independently monitor both locations of this multisite trial every ten patients. This data monitoring is performed by a clinical research associate (CRA). His/her role is to check the consent form, the quality of data collection (missing data, data entry errors …), the availability of treatment at each site, the pharmacy process, and the declaration of any serious adverse event. He/she is employed by the sponsor but is independent of the investigators and is not involved in carrying out the study or interpretation of the results. Anonymized data are only accessible to the investigators, the sponsor, and other authorized persons (statistician, data manager …). They will be stored confidentially for 15 years by the sponsor. They will not be used for further studies without further patient agreement. At the end of the study, we plan to communicate trial results to participants, healthcare professionals and the public via a peer-reviewed publication. Authors will be considered in the case of a substantial contribution to the conception or design of the study or the acquisition, analysis or interpretation of data. They will need to have drafted the work or revised it critically. They will all approve the final version to be published. We do not expect the participation of a professional writer. Data not disclosed in the publication will not be accessible.

### Intervention protocols

During the post-partum period, patients are usually followed by midwives. In case of headache, whether an accidental dural puncture is diagnosed or not, the anaesthesiologist is informed by the midwives. Therefore, any symptomatic patient is examined by an anaesthesiologist. The study investigators are the anaesthesiologists working in the maternity department of the two centres.

Patients are enrolled when diagnosed with PDPH based on the anaesthesiologist’s clinical evaluation. They are randomised to receive intravenous tetracosactide or placebo. In the study group, patients receive a single intravenous injection of 1 mg tetracosactide (Synacthen®, Sigma-Tau laboratory, Roma, Italy). Four vials containing 0.25 mg tetracosactide (in 1 ml of solvent) are reconstituted in 100 ml of normal saline (0.9% NaCl). This solution is infused intravenously over 20 min. In the control group, patients receive an equal volume of normal saline: 104 ml over 20 min. The whole intervention is administered over a 20-min course and therefore is not modifiable once begun except for the occurrence of a side effect. A side effect is defined herein as any new abnormality observed upon clinical examination, occurring during the injection. In this case, the treatment is immediately stopped but monitoring and data collection continues.

Standard analgesic medication, as concomitant treatments, is also initiated in both groups from the beginning of headache, as follows:
for mild headache (NRS < 3/10): 1 g paracetamol and 400 mg ibuprofen orally every 6 hfor moderate headache (NRS = 3): nefopam 20 mg and/or a combination of paracetamol 300 mg and opium 10 mg is given in addition every 4 hfor severe headache (NRS ≥ 4): morphine 10 mg orally every 4 h can be added as required

These treatments are adjusted daily.

The primary and secondary endpoint, including tolerance criteria, are evaluated blinded during infusion of the study treatment, 2–6 h later, 1 day, 2 days, 3 days and between 13 and 17 days post-treatment by the investigator. The latter is conducted by phone call in order to increase the complete follow-up. The total duration of the study is therefore 13 to 17 days. Any alternative analgesic intervention required after receiving the study treatment is reported at each time point as indicated above. The study timeline is summarised in Fig. 2.

**Fig. 2 Fig2:**
[figure not shown]
Schedule of enrolment, intervention and assessment

Epidural blood patch is performed for patients who reported a persistent moderate to severe headache a minimum of 24 h after administration of the study treatment and 36 h after the dural puncture, based on the clinical appreciation of the anaesthesiologist. Epidural blood patch can be repeated twice if required (i.e., if the headache does not improve or if it increases again). The anaesthesiologist performs the epidural blood patch. Autologous blood is injected into the epidural space using an 18-gauge Tuohy needle. The injection is stopped when the patient feels pressure in the lower back or pain.

### Statistical analysis

Unblinding occurs at the end of the study and once the database has been frozen. Analyses will be carried out on an intention-to-treat (ITT) basis. If data are missing from visits, we will carry forward the last value for which the pain (and other symptoms) has not improved. This is the most pessimistic scenario for this condition, which usually improves spontaneously. Blood patch can only be performed at the hospital, and it is therefore very unlikely that there will be missing data regarding the primary endpoint. If a patient does not receive full treatment, she will be included in the group to which she was randomised for further ITT analysis. Statistical analyses will be performed using IBM SPSS statistics for windows (IBM corp., Armonk, NY, USA) and R (R Foundation for Statistical Computing, Vienna, Austria). All data will be checked for normal distribution using the Kolmogorov test. For normally distributed data, variables will be presented as mean ± standard deviation (SD). Non-normally distributed data will be presented as the median and interquartile range [IQR]. Categorical variables will be presented as number and percentage of the total. To compare the two groups (tetracosactide and placebo), we will use Fisher’s exact test for qualitative data and the non-parametric Mann-Whitney tests for quantitative variables. A comparison of the two groups at randomisation will identify potential bias due to unequal allocation. A multivariate logistic regression analysis will be performed to study factors independently associated with the response to tetracosactide and to control potential confounding factors.

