#### Intermediate analysis

The hypothesis of a 30% difference between the two groups is conservative compared to the 50% reduction reported by Hakim [39]; a difference of only 30% between the two groups should already be clinically relevant. An interim analysis is therefore planned after the enrolment of 44 patients. The overall alpha risk will be adjusted according to the Bonferroni method and will be 2.5% (5% / 2). A *p* value < 0.025 will therefore be considered statistically significant. If this initial analysis is statistically significant (*p* < 0.025), the independent monitoring committee may decide to stop the study without waiting for the planned recruitment. Otherwise, the study will be continued until the inclusion of 88 patients.

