## Trial status

The fourth protocol version dated 28 September 28 is in place. The study is ongoing; the first patient was included in October 2016, and in May 2019, 25 patients had been enrolled. Initially we expected to finalise the study in October 2018, but we had to extend the inclusion phase until 2021 to reach a total of 88 inclusions. Due to the ongoing nature of the study and to avoid influencing its conduct, the final results are not presented herein. An intermediate analysis will be performed after 44 inclusions, and if a significant difference is observed between the two groups concerning the primary outcome, the study will be discontinued.

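### Fisher's exact test leaves part of each look's 2.5% alpha unused; Boschloo's exact test at the same level would gain about 1 to 5.5 points of final-analysis power at 90% vs 60%, depending on the arm split, with no extra patients

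*Protocol article*

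**What the plan says.** The primary endpoint is binary. Under Primary endpoint the rate is "the number of patients who receive a blood patch within the 15-day period divided by the total number of participants included".

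The only unadjusted test named for such data is in Statistical analysis: "we will use Fisher’s exact test for qualitative data". A multivariate logistic regression is added there, to study factors associated with response and to control confounding.

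The sample size in Number of patients needed rests on the same test: "α = 2.5% Fisher’s exact test, power of 80%, p1 = 0.9; p2 = 0.6". It leads to 44 women per group, and "Thus a total of 88 patients need to be randomised".

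Intermediate analysis halves 5% by Bonferroni. It applies a threshold of 0.025, with one interim look after 44 patients and a final look at 88. Sidedness is not stated. Statistical analysis names R as well as SPSS.

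**The concern.** Fisher's test conditions on the total number of women patched. With a few dozen women per arm the conditional distribution has few attainable p-values, so the test usually stops well short of its nominal level. The plan has already paid for its alpha by halving 5%, and the discreteness of the test then leaves part of each half unspent.

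This matters because power is the trial's acknowledged weak point. The Discussion warns that the sample may be too small if the control patch rate is below 90%. Recruitment is slow: under Trial status, "in May 2019, 25 patients had been enrolled", against a target of 88 and a start in October 2016. A test that recovers some power from the same women, with the same guarantee at each look, is worth considering.

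**Working it through.** **Inputs.** From Number of patients needed: 44 per arm, control rate 0.9, active rate 0.6, alpha 0.025, power 0.80. From Intermediate analysis: p < 0.025 at each look, interim at 44 women (22/22 if the arms are equal). Assumption: the tests are two-sided. This fits the plan's figure, as shown in step 1.

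**Formulas.** Let x of n1 control women and y of n2 active women receive a patch, and let pF(x, y) be the two-sided Fisher p-value (the sum of conditional table probabilities no larger than the observed one).

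- Power = Σx Σy Bin(x; n1, p1) · Bin(y; n2, p2) · 1[pF(x, y) ≤ c]
- Size = the maximum over a common rate p of the same sum with p1 = p2 = p
- Fisher: c = 0.025
- Boschloo: c is the largest cut-off for which the size stays ≤ 0.025

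Fisher's own size is below 0.025, so Boschloo's cut-off cannot be smaller than Fisher's. Every table rejected by Fisher is therefore rejected by Boschloo. The enumeration confirmed this at each split below.

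**Step 1: reproduce the plan.** Two-sided Fisher at 0.025, 90% vs 60%, gives 79.6% power at 42 per arm, 81.1% at 43 and 81.1% at 44. The stated 44 with 80% power is confirmed. A one-sided test at 0.025 would have needed only 36 per arm, which is why two-sided is assumed.

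**Step 2: final analysis** (control/active split, 90% vs 60%).

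| Split | Fisher size | Boschloo size | Fisher power | Boschloo power | Gain (points) |
|---|---|---|---|---|---|
| 44/44 | 1.47% | 2.46% | 81.1% | 86.6% | 5.5 |
| 43/45 | 1.89% | 2.49% | 84.1% | 86.3% | 2.2 |
| 45/43 | 1.89% | 2.49% | 85.3% | 86.9% | 1.6 |
| 42/46 | 1.90% | 2.41% | 84.2% | 86.7% | 2.5 |
| 46/42 | 1.90% | 2.41% | 84.3% | 85.1% | 0.8 |

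At 44/44 the cut-off on Fisher's p-value moves from 0.025 to about 0.0385. For example, 40/44 vs 31/44 has Fisher p = 0.029 (not significant) and Boschloo p = 0.016 (significant).

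**Step 3: lower control rates, 30-point difference, 44/44.** At 80% vs 50% power goes from 71.4% to 76.8%, and at 75% vs 45% from 67.5% to 74.0%. Over the five splits in the table the gain at these rates is about 2 to 6.5 points.

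**Step 4: interim, 90% vs 60%.**

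| Split | Fisher power | Boschloo power | Gain (points) |
|---|---|---|---|
| 22/22 | 42.2% | 54.6% | 12.4 |
| 23/21 | 47.7% | 53.9% | 6.2 |
| 21/23 | 49.1% | 49.9% | 0.8 |

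At 22/22 Fisher's size is 1.10% and Boschloo's 2.44%.

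**Step 5: both looks together** (22/22, then 44/44). The chance of success at 90% vs 60% is 82.3% with Fisher at both looks and 87.9% with Boschloo at both. Maximum overall type I error is 2.2% and 4.1%. Both lie under the planned 5%.

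**The case against.** The strongest reply is that nothing here is wrong. The trial is sized and analysed with the same test at the same threshold, and the planned power is delivered. That stands. A reader might infer that Fisher's test is invalid here or that 88 is miscalculated; the protocol's own figures, reproduced in step 1, show neither.

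A second reply is that the gain depends on the split. This also stands. Randomisation is in blocks stratified by two sites, and the article gives no block size, so unfinished blocks can leave the arms unequal at 44 or 88 women. Moving one woman between arms lifts Fisher's size to 1.89% and cuts the gain at 90% vs 60% to about 2 points. A reader might take the 5.5 points at 44/44 as general; it is not.

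Nor can the gain be turned into a saving of ten women, from the fact that Fisher needs 49 per arm to match Boschloo at 44/44. That comparison holds only for equal arms: Fisher reaches 86.9% at 46/45 (91 women) and 84.5% at 45/46.

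Third, the larger rejection region has a price. Overall type I error rises within its budget, and an early stop at 44 women becomes easier. Some would prefer a conservative interim, so the interim gain is a trade-off and not purely a benefit.

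Fourth, the change does not remove the risk named in the Discussion. At 75% vs 45% Boschloo still gives only 74.0% at 44/44, short of 80%.

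These replies limit the size of the point. They do not remove it: the gain was positive at every split and rate checked, and each look stays within 2.5%.

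**Conclusion.** The point holds as an efficiency gain. At two-sided 0.025 and 90% vs 60%, replacing Fisher's test by Boschloo's adds 5.5 points of power at the planned 44/44 split and about 1 to 2.5 points at splits from 43/45 to 46/42. At 80% vs 50% and 75% vs 45% it adds about 2 to 6.5 points. At the interim it adds about 1 to 12 points.

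The assumptions are two-sided testing, the plan's rates or a 30-point difference at lower control rates, and no missing primary outcomes, which the protocol calls very unlikely. If the test were one-sided at 0.025 the direction would be the same: 87.9% to 92.0% at 44/44.

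**What to change.** Before the interim analysis, and while the data are blinded, name Boschloo's unconditional exact test as the test of the blood patch rate. State that it is two-sided, at 0.025 per look, computed for the arm sizes actually observed, and run in R. Report Fisher's p-value beside it as supportive. If a conservative interim is wanted, Fisher can stay at the interim with Boschloo at the end only: power over both looks at 90% vs 60% (22/22, then 44/44) is then 87.2%, against 87.9% with Boschloo at both.

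The costs are a documented and justified amendment to the primary analysis of a trial already under way, a test that clinical readers know less well, and a maximum overall type I error that rises from about 2.2% to 4.1%, still within 5%. No further patients or data are needed.
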